### Outcome measures

#### Primary outcomes

The primary outcomes of our study are the Constant-Murley score (CMS) and visual analog scale (VAS). The shoulder function of the patients will be measured by adopting CMS. CMS is a self and examiner based tool, including pain, the activity of daily life, range of motion, and muscle strength [26]. The total score is 100 and divide into four levels, excellent (< 11), good (11–20), fair (21–30), and poor (> 30) [27]. The overall shoulder pain will be assessed through a VAS, with a score of 0 (no pain) to 10 (maximal pain).

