## Methods

### Study design

A single-center, prospective non-randomized study with 12 months follow-up duration was designed. The study has started in July 2019 and is ongoing. Three hundred-forteen patients with rotator cuff injury aged over 18 are enrolled and divided into two groups. The participants need to visit a physical therapist 2 days before PRP injection, 1 months, 3 months, 6 months, and 12 months after rehabilitation programs. The feasibility and preciseness of the whole process are supervised by 1 to 2 supervisors.

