#### Secondary outcomes

Tear size change assessed by MRI, the quality of life evaluated by Medical Outcomes Study Short Form 12-Item (SF-12), and adverse events will be recorded as secondary outcomes. An independent radiologist will assess tear size through MRI before PRP injection and 12 months follow-up. The SF-12 is a 12-item questionnaire, focusing on physical functioning, social functioning, bodily pain, vitality, role physical, role emotional, general health, and mental health [28]. In addition, any adverse events caused by PRP injection and physiotherapy will be recorded via self-report. The outcome indicators will be assessed at five different times by a blinded physiotherapist (Table 1).

**Table 1 Tab1:** Schedules for follow-up assessments and data collection

Assessments	Baseline (Two days after PRP injection)	Finish manual therapy			
		1 month	3 months	6 months	12 months
CMS	√	√	√	√	√
VAS	√	√	√	√	√
SF-12	√				√
Adverse effects	√	√	√	√	√
Tear size	√				√

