### Data management

All the involved participants were coded with a number. We used a case report form (CRF) to record the information of participants, including basic information, shoulder function scores, MRI results, and follow-up. The follow-up duration of each participant will be at least 1 year. We also assessed the shoulder function at four other points, two days after PRP injection, 1 month, 3 months, and 6 months. When participants come back to our hospital for a check, the data will be collected by a blinded physiotherapist, other researchers will be forbidden from obtaining the research data. Besides, statisticians will be blinded in our study.

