### Sample size calculation

We used the Constant-Murley score serving as a basis of estimating sample size. Based on the study of Sham et al. [12] and our pilot observations, we consider that the change of Constant score could be 8 with a standard deviation of 20. We calculate that 131 participates for each group will be required with alpha set at 0.05 and a power of 0.8. Considering the 20% drop rate, we will recruit 314 participates in total.

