### Statistical analysis

All statistical analyses will be performed using SPSS 25.0 (IBM Corporation, Armonk, NY). Continuous variables are described as means and standard deviation. We will use independent *t* tests or Mann-Whitney *U* tests to compare 2 groups. If needed, the stratified analysis will be conducted based on the age of participants and the PRP injection site. A *P* value < .05 will be defined as statistically significant.

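### Two primary outcomes are measured at four follow-up visits, with no primary visit and no success rule, so the stated 0.05 does not fix the primary error rate

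*Protocol article*

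**What the plan says.** The Primary outcomes section names two: "The primary outcomes of our study are the Constant-Murley score (CMS) and visual analog scale (VAS". It does not rank them or attach a time point.

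On timing, the Secondary outcomes section states: "The outcome indicators will be assessed at five different times by a blinded physiotherapist (Table 1". Table 1 ticks CMS and VAS at baseline and at every later visit. The Study design section puts the follow-up visits at "1 months, 3 months, 6 months, and 12 months after rehabilitation programs".

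The Data management section comes closest to a main time point. It sets follow-up at a year or more and adds: "We also assessed the shoulder function at four other points, two days after PRP injection, 1 month, 3 months, and 6 months". It does not use the word primary for any visit.

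The Statistical analysis section plans independent t tests or Mann-Whitney tests between the two groups and sets one threshold: "A *P* value < .05 will be defined as statistically significant". The Sample size calculation rests on one outcome: "We used the Constant-Murley score serving as a basis of estimating sample size". It assumes a change of 8 with SD 20, alpha 0.05 and power 0.8, and names no visit. VAS is not sized.

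**The concern.** A primary endpoint is a variable at a time, together with a statement of what counts as success. Here the variable is doubled, the time is open and the success rule is absent. The sample size is built on a single test at alpha 0.05, yet nothing in the article confines the primary claim to a single test.

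The open visit matters because the candidates answer different questions. Manual therapy lasts three weeks and home exercise three months, so the 1-month visit follows manual therapy, the 3-month visit falls near the end of home exercise, and 12 months shows durability. Any of them could later be presented as the main result, for either score. A favourable report could then rest on the best of several comparisons while quoting an error rate that belongs to one.

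**Working it through.** **1. The plan's own figure.** For two means, n per group = 2 × [SD × (z for alpha + z for power) / difference]².
- Two-sided 0.05, power 0.80: 2 × [20 × (1.960 + 0.842) / 8]² = 98.1, so 99 per group, not the stated 131.
- Two-sided 0.05, power 0.90: 131.3 before rounding, which is close to 131.

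The stated size therefore fits 90% power for one CMS test. That mismatch is a separate matter. It is relevant here only because it leaves room for an alpha split (step 5).

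**2. Independent tests (upper reference).** The chance of at least one false P < .05 among m tests is 1 − 0.95^m.
- Either outcome at one visit, m = 2: 1 − 0.9025 = 9.75%.
- One outcome at any of four visits, m = 4: 18.5%.
- Either outcome at any of four visits, m = 8: 33.7%.

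**3. Correlated tests.** The tests are not independent: visits are repeated measures on the same patients, and CMS contains a pain component. The article gives no correlations, so these are assumptions. Eight null z-statistics (2 outcomes × 4 visits) were simulated 1,000,000 times. All pairs of visits had the same correlation, and each outcome was oriented so that positive means benefit.

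| Correlation between visits / between outcomes | Any of 8, two-sided | Any of 8, favouring physiotherapy | Either outcome, one visit, two-sided |
|---|---|---|---|
| 0 / 0 | 33.7% | 18.3% | 9.7% |
| 0.3 / 0.3 | 31.0% | 16.0% | 9.5% |
| 0.5 / 0.5 | 26.9% | 13.6% | 9.1% |
| 0.7 / 0.5 | 22.7% | 11.4% | 9.1% |
| 0.7 / 0.7 | 20.8% | 10.4% | 8.3% |
| 0.8 / 0.8 | 17.2% | 8.6% | 7.8% |
| 0.9 / 0.9 | 12.9% | 6.4% | 7.1% |

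The two-sided columns compare with 5%, the favourable-only column with 2.5%.

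**4. If both outcomes had to succeed.** At one fixed visit, the chance that both are falsely significant is 0.25% to 3.0% over the same range, so there is no inflation. The article does not set this rule.

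**5. Room for a split.** With two outcomes at one visit and 0.025 each, CMS needs 119 per group for 80% power under the stated 8 and SD 20. With 131 per group the standard error is 20 × √(2/131) = 2.47, and power is Φ(8/2.47 − 2.241) = 84%. If 20% of 314 are lost, 314 × 0.8 / 2 = 125.6 per group remain and power is 82%. Splitting over all eight tests (0.00625 each) would need 160 per group, and 131 would give 69%.

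**The case against.** **Testing at every visit is not stated.** Table 1 is a data-collection schedule, and the Statistical analysis section says only that two groups are compared. This stands. A reader might infer that the plan commits to eight primary tests at 5% each, with a 34% error rate. The article does not say so: eight tests is an inference from the schedule and from the absence of any single visit or repeated-measures model, and 34% is the independence case, not an expected value.

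**The Data management section points to 12 months.** It sets follow-up at a year or more and calls the earlier assessments other points. This also stands as a lean, and on that reading the either-outcome rate is 7-10%, not 13-34%. It falls short of naming a primary visit, and the sentence concerns shoulder function, not VAS.

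**The percentages count both directions.** The hypothesis is that adding physiotherapy has an advantage, so a false success is a favourable false positive. A reader might take the two-sided figures as the chance of wrongly declaring physiotherapy better. They are not; that chance is about half as large. The ratio to nominal is still material.

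**An analysis plan that is not shown may handle multiplicity.** It may well set the adjustment method, and the lack of one in a journal article is no fault in itself. Which visit is primary, and whether one or both outcomes must succeed, belong to the definition of the primary outcome, which this article does set out. It does so with two outcomes, one blanket threshold and a sample size for a single test.

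**Conclusion.** The point holds in a limited form. The plan has two primary outcomes, four follow-up visits, no primary visit, no rule on one or both, and one unadjusted P < .05.

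The size depends on the reading:
- both outcomes required at one fixed visit: no inflation;
- either outcome at one visit: about 7-10% two-sided;
- any outcome at any visit: about 13-34% two-sided, or about 6-18% in favour of physiotherapy against 2.5%.

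The ranges rest on assumed correlations from 0.9 down to 0 and, for the last reading, on the inference that every visit is tested. The article does not settle which reading applies, and that is the defect. It should be corrected. Correcting it will not address the confounding that comes from patients choosing their own group, which is a separate limitation that no alpha rule can repair.

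**What to change.** Before any between-group comparison is seen, record in a dated amendment:

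1. One primary outcome at one visit, for example CMS, on which the trial is sized, at 12 months, the end of follow-up. The investigators may justify another visit; what matters is that it is named in advance.
2. The rule for VAS at the same visit. Either test it at 0.05 only if CMS is significant (fixed sequence) or, if either outcome is to count, test each at 0.025.
3. That CMS and VAS at the other visits are secondary and reported with confidence intervals.
4. Which visit the 8-point assumption came from and, if that is not the primary visit, a statement to that effect. The Sample size calculation ties the figure to no visit, so it should not simply be relabelled.

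**Cost.** No added patients or visits. Under the fixed sequence CMS keeps full alpha; VAS is confirmatory only if CMS succeeds, so it loses some power. Under the split, CMS power falls from about 90% to about 84% at 131 per group, assuming equal groups, which patient choice does not guarantee. VAS power cannot be computed because the article gives no VAS inputs. Because the study is registered and under way, the amendment is credible only if its date clearly precedes any look at group differences.

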#### Secondary outcomes

Tear size change assessed by MRI, the quality of life evaluated by Medical Outcomes Study Short Form 12-Item (SF-12), and adverse events will be recorded as secondary outcomes. An independent radiologist will assess tear size through MRI before PRP injection and 12 months follow-up. The SF-12 is a 12-item questionnaire, focusing on physical functioning, social functioning, bodily pain, vitality, role physical, role emotional, general health, and mental health [28]. In addition, any adverse events caused by PRP injection and physiotherapy will be recorded via self-report. The outcome indicators will be assessed at five different times by a blinded physiotherapist (Table 1).

**Table 1 Tab1:** Schedules for follow-up assessments and data collection

Assessments	Baseline (Two days after PRP injection)	Finish manual therapy			
		1 month	3 months	6 months	12 months
CMS	√	√	√	√	√
VAS	√	√	√	√	√
SF-12	√				√
Adverse effects	√	√	√	√	√
Tear size	√				√

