### Study setting and participants

This study is being performed in the Affiliated Hospital of Southwest Medical University in China, and all participants are recruited from inpatient and outpatient. All patients were screened rigorously according to inclusion and exclusion criteria. Physicians decide whether the patient is enrolled, and they will tell eligible participants the research protocol in detail. Every eligible participant will be asked to sign a written consent before taking part in this study. The participants voluntarily choose to receive rehabilitation programs after PRP injection, then PRP in addition to physiotherapy group and PRP group were formed. The trial protocol is shown in Fig. 1.

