### Physiotherapy protocol

Physiotherapy will be conducted 2 days after PRP injection in the experiment group. Manual therapy, including joint mobilization, soft tissue massage, and manipulation will be implemented for three weeks, three sessions/week. Meanwhile, supervised exercise therapy in the hospital third a week for three weeks. Home exercise will be carried out once a day and last for three months. The experiment group consists of six exercises: stretching program (crossover arm stretch, sleeper stretch, and anterior shoulder stretch), posture adjustment (scapular retraction, scapular shrug), and strengthening exercise (bilateral external rotation). For crossover arm stretch, patients sit on a chair with good posture, uninvolved side holds the upper arm of the affected arm and pull it across the chest as far as they can; sleeper stretch, patients lie on the affected shoulder side with shoulder and elbow flexion at 90^o^, then use unaffected side to push it down. Hold in the position when patients feel tight in the upper back of the shoulder; anterior shoulder stretch, patients should stand by the door with shoulder abduction and elbow flexion, put the palm on the door, subsequently, lean forward until patients feel a stretch in the front of the affected shoulder; scapular retraction, patients should lie on stomach on a bed with the affected arm hanging over the side, and keep they elbow straight by squeezing shoulder blade toward the opposite side, afterwards, return slowly and repeat; scapular shrug, the participants should abduct shoulder at 10 ^o^ − 20 ^o^ with the palm facing forward, and then shrug shoulder with resistance band; bilateral external rotation, an exercise for rotator cuff and scapula stabilizers, patients stand against the wall holding a resistance band by two hands with shoulder abduction 0^o^ and elbow flexion 90^o^, later, pull the band as far as possible without unnecessary movement. The details of six exercises are listed in Additional file 1: Appendix A.

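### The protocol's only recording rule for adverse events covers those caused by treatment, so cause is judged before recording and the filter is not neutral between arms

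*Protocol article*

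**What the plan says.** Under Secondary outcomes, the protocol article first names the outcome without restriction: "adverse events will be recorded as secondary outcomes". The same paragraph then gives the recording rule: "any adverse events caused by PRP injection and physiotherapy will be recorded via self-report". It states no criterion for cause and names nobody other than the self-reporting participant to judge it.

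The next sentence reads "The outcome indicators will be assessed at five different times by a blinded physiotherapist". Table 1, captioned "Schedules for follow-up assessments and data collection", ticks adverse effects at baseline and at 1, 3, 6 and 12 months, in one schedule that is not split by arm. Data management adds that at return visits "the data will be collected by a blinded physiotherapist".

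Two other sections bear on the point. Study setting and participants says "The participants voluntarily choose to receive rehabilitation programs after PRP injection", so each participant knows which treatment they have. Physiotherapy protocol gives the experiment arm a course that controls do not have: "Manual therapy, including joint mobilization, soft tissue massage, and manipulation will be implemented for three weeks, three sessions/week".

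**The concern.** A comparison of harms between arms is interpretable when events are captured in the same way in both and relatedness is decided afterwards. Here relatedness is the entry condition. Three things follow.

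- An event that the participant blames on something else, such as ordinary activity, age or another illness, need never be written down. A real signal that nobody recognises as treatment-related would not appear in the data.
- The entry condition differs by arm, because a control receives no physiotherapy and so cannot have an event attributed to it. Shoulder soreness put down to exercise in the experiment arm qualifies. The same soreness in a control qualifies only if it is put down to the injection.
- To apply the rule, the blinded collector has to hear whether physiotherapy was given. The blinded physiotherapist is also the stated assessor of the outcome indicators, and Primary outcomes describes the Constant-Murley score as partly examiner-based. The wording therefore puts pressure on the blinding of a primary outcome too.

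**Working it through.** The plan states no adverse event rate, so there is no figure to reproduce. The check consists of reading the rule through, counting contacts and giving one conditional illustration.

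**1. The filter.** Suppose there is no true difference: an event unrelated to treatment occurs with probability b in each arm. Let a be the chance that the participant attributes it to the injection (taken as equal in both arms), and p the further chance that an experiment participant attributes it to physiotherapy.

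- Recorded in controls: b × a
- Recorded in the experiment arm: b × (a + p)
- Spurious difference: b × p
- Events never recorded: b × (1 − a) in controls and b × (1 − a − p) in the experiment arm

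The spurious difference vanishes only if p = 0. If every event is recorded regardless of cause, both arms show b and nothing is lost. The document gives no value for b, a or p. The sign is not certain either: people who chose physiotherapy may be reluctant to blame anything on their treatment, and a would then differ between arms.

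**2. Scheduled checks.** Table 1 gives 5 adverse-effects checks per participant in each arm, so 5 versus 5.

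**3. Extra contacts in the experiment arm.** Manual therapy: 3 per week × 3 weeks = 9. Supervised hospital exercise runs over the same three weeks. Its frequency is garbled in the text and is read here, as an assumption, as three times a week: 3 × 3 = 9. If it shares visits with manual therapy, there are 9 extra contacts and the total is 5 + 9 = 14. If the visits are separate, there are 18 extra and the total is 5 + 18 = 23. No section says that adverse events are collected at these sessions, and none limits self-report to the five visits.

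**4. What session reports would do, if they counted.** Assumptions, none of them from the document: 10% of participants in each arm truly have an event, and each contact detects it independently with probability q. Proportion recorded = 0.10 × (1 − (1 − q)^contacts).

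| q | Control, 5 contacts | Experiment, 14 contacts |
|---|---|---|
| 0.1 | 4.1% | 7.7% |
| 0.2 | 6.7% | 9.6% |
| 0.3 | 8.3% | 9.9% |
| 0.5 | 9.7% | 10.0% |

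The artefact runs from 7.7 − 4.1 = 3.6 percentage points when detection is poor to 10.0 − 9.7 = 0.3 when it is good. It is zero at every q if only the Table 1 visits count.

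**The case against.** The strongest reply has five parts.

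- **The restriction may be loose wording.** The preceding sentence and Table 1 name adverse events or effects without a causal qualifier, so the contested sentence might be meant to describe only the route, self-report. That is possible. Still, it is the only sentence that says which events are captured, and site staff following it would apply the filter.
- **Detail may sit in a fuller protocol.** A journal article can leave out attribution criteria and form fields, and their absence is not the point here. The point is a rule that the article does state.
- **Extra harm from extra treatment is a real difference.** This stands: an event truly caused by physiotherapy belongs in the comparison. It does not answer the case of a background event that can be attributed to physiotherapy in one arm only.
- **Ascertainment is equal.** A reader might infer from the nine sessions that the experiment arm has 14 chances to report against 5. The document does not support this. Table 1 gives both arms the same five checks, and the sessions are described as treatment only. The inference also needs an assumed detection rate. What remains is an ambiguity.
- **Collection is blinded, and key harms are measured elsewhere.** Calling the process simply unblinded would be wrong: the reporter knows the arm, but the stated collector is blinded. Nor would worsening of the tear be lost. MRI tear size is measured in all participants before injection and at 12 months regardless of cause, while pain and function are scored at all five times. What the filter puts at risk is events outside those measures.

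It is also fair that the stated aim covers pain, function, tear size and quality of life, and that no test on adverse events is specified. This limits the weight of the point.

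**Conclusion.** The point holds as a fault in a stated recording rule for a secondary outcome. As written, events are screened for cause before capture, by participants who know their arm, and the screen admits two causes in one arm and one in the other. It also sits badly with the blinded collector. The resulting arm difference would mix harm with attribution, and unattributed events could go unrecorded.

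Its size cannot be computed, because the document gives neither event rates nor attribution rates. Unequal ascertainment is a conditional risk: nil if only the Table 1 visits count, and about 0.3 to 3.6 percentage points under the assumed 10% true rate, q from 0.1 to 0.5 and 14 contacts.

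The verdict assumes that the sentence is applied literally and that no fuller document overrides it. The primary comparison is touched only through the possible loss of assessor blinding. The change should be made because it is cheap and because the article describes the study as ongoing: events not recorded now may not be recoverable later.

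**What to change.** Replace the recording sentence with a rule that:

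1. every adverse event is recorded whatever its presumed cause, in answer to the same fixed question at the five Table 1 visits in both arms;
2. relatedness to the injection or to physiotherapy is assigned afterwards in a separate field, by someone other than the blinded physiotherapist;
3. the between-arm comparison uses events elicited at those five visits, and any events reported at physiotherapy sessions are listed separately.

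The rule depends on the visits meaning the same thing in both arms. Study design places the first visit two days before the injection, whereas Table 1 and Data management place it two days after. Study design also counts follow-up from the end of rehabilitation, which gives controls no starting point. These passages must be reconciled.

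The cost is one protocol sentence and one case report form field, with existing visits and no change to treatment. The downside is slightly more events to log. Participants may still mention physiotherapy to the collector, so the change removes the need to unblind but not every chance of it.

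### The blinded physiotherapist who scores the CMS is also given the collection of physiotherapy-related adverse events, with no stated separation, so an individual report can reveal the arm

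*Protocol article*

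**What the plan says.** - **Primary outcomes:** "The primary outcomes of our study are the Constant-Murley score (CMS) and visual analog scale (VAS"). The CMS depends partly on the examiner: "CMS is a self and examiner based tool, including pain, the activity of daily life, range of motion, and muscle strength".
- **Secondary outcomes:** "adverse events will be recorded as secondary outcomes", and their content is defined as "any adverse events caused by PRP injection and physiotherapy will be recorded via self-report". The same section then states "The outcome indicators will be assessed at five different times by a blinded physiotherapist (Table 1").
- **Table 1:** the row "Adverse effects" is ticked at baseline and at 1, 3, 6 and 12 months, exactly as CMS and VAS are.
- **Data management:** at return visits "the data will be collected by a blinded physiotherapist, other researchers will be forbidden from obtaining the research data".
- **Physiotherapy protocol:** physiotherapy is given in the experiment group only, from 2 days after the injection. Manual therapy and supervised exercise last three weeks and home exercise three months.
- **Study setting and participants; Discussion:** participants choose their own group, and the limitations concede that therapists cannot be blinded.

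**The concern.** Patients know their group because they chose it, and the treating therapists know it too. For range of motion and strength, the examiner-rated parts of the CMS, the main safeguard against biased scoring is that the examiner does not know the group. The article appears to give that examiner a second task that works against the safeguard: taking reports of events caused by a treatment that only one group receives. A PRP event reveals nothing, since both groups are injected. A physiotherapy event can come only from the experiment group, so any disclosure runs in one direction. If an examiner who has learned the group scores more favourably, the error falls on a primary outcome, the one on which the sample size is based, and in the direction of the study hypothesis.

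**Working it through.** The plan states no figure on this point, so there is none to reproduce. The check sets the sections side by side.

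**1. Does the blinded assessor's task include adverse events?** Count the ticks in Table 1: CMS 5, VAS 5, adverse effects 5, SF-12 2, tear size 2. The sentence on five assessment times fits three rows exactly, and adverse effects is one of them. Tear size is taken out of the physiotherapist's task explicitly, because Secondary outcomes gives it to an independent radiologist. No such exception is made for adverse events.

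**2. Could someone else take the report?** Secondary outcomes says only that events are self-reported and does not name the recipient. Data management names the blinded physiotherapist as collector of visit data and keeps other researchers away from the data. Read together, these make the assessor the recipient. No section separates safety reporting from scoring.

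**3. Does a report reveal the group?** It does if the event is recognisably due to physiotherapy. The definition itself asks for events attributed to physiotherapy, a treatment whose use the recorder is not supposed to know. Such complaints are foreseeable, since Physiotherapy protocol prescribes pendulum exercise for patients who have discomfort after the six exercises.

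**4. At which visits?** Physiotherapy starts at about the time of the baseline column, so baseline adds little. Counted from the injection, the 1-month visit falls within the three months of home exercise and the 3-month visit at its end. Counted from the end of the three-week manual therapy, the 1-month visit comes about 3 + 4 = 7 weeks after the start, still within home exercise, and the 3-month visit shortly after it ends. New physiotherapy events at 6 and 12 months are unlikely. Knowledge gained earlier can carry over to those visits if the same person scores or earlier records are visible; the article settles neither.

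**5. How large could the effect be?** With f the proportion of the experiment group revealed by a report, and b the shift in CMS when the examiner knows the group, the bias in the group mean is f × b. The documents give neither input, so the following is assumption only:
- f from 5% to 30%, b from 2 to 10 points: 0.05 × 2 = 0.1 to 0.30 × 10 = 3.0 points. Against the 8-point difference in Sample size calculation, 0.1/8 = 1% to 3.0/8 = 38%.
- f from 20% to 60%, b from 2 to 4 points: 0.20 × 2 = 0.4 to 0.60 × 4 = 2.4 points, or 0.4/8 = 5% to 2.4/8 = 30%.

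The result only returns what is put in. It also overstates what safety reporting adds, because f should count only participants who would not have disclosed their group in some other way.

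**The case against.** The strongest reply is that the article never says the assessor questions patients about side effects. Self-report may mean a form that the assessor does not see, and who receives forms, in what order, is detail that a journal article often leaves to the full protocol. This stands in part: if such a form exists, one sentence settles the matter. It does not remove the point, which rests on what is written. Two sections assign outcome and visit data to the blinded physiotherapist, and one shuts others out.

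Several further limits stand in full.
- A reader might infer that safety reporting unmasks the assessor for the experiment group as a whole. The documents do not support that. Only participants who report a recognisable physiotherapy event are revealed, and soreness alone is weak evidence: every participant enters with at least three months of shoulder pain and receives an injection.
- A reader might also infer that every row of Table 1 belongs to one person. Tear size does not, and the text does not say that the same physiotherapist attends every visit.
- Safety reporting is only one route to disclosure. Patients may mention their treatment at any examination.
- VAS and the self-rated CMS items come from patients who know their group, whatever the assessor knows.

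**Conclusion.** The concern holds as a risk to blinding. As written, the examiner who scores the CMS also collects events that can identify the experiment group, on the same visit schedule and with no stated separation. The exposure is limited to the examiner-rated parts of the CMS, to participants who report a recognisable physiotherapy event, and mainly to reports at 1 and 3 months, with possible carry-over to later scoring. Carry-over assumes continuity of the assessor or access to earlier records.

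It would go too far to conclude that blinding is defeated, or to attach a percentage bias to the treatment effect. The documents contain no adverse-event rate, no measure of how scoring changes once the group is known and no evidence on its direction, so the size cannot be estimated. This is a worthwhile, inexpensive improvement, not a flaw that invalidates the primary analysis.

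**What to change.** In Secondary outcomes and Data management, state that:
- the assessor scores CMS and VAS first, does not ask about treatment or side effects, and has no access to adverse-event records from the current or earlier visits;
- adverse events are collected in the same way in both groups, either on a patient-completed form that bypasses the assessor or by the enrolling physician. The treating therapist is not suitable, because controls have none and ascertainment would differ between groups;
- the rule in Data management that keeps other researchers from the data has an exception for whoever handles the adverse-event reports.

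If self-report already works through a form the assessor never sees, saying so and adjusting the access rule is enough. The cost is a small change to the visit sheet and a few minutes of existing staff time per visit, with no new staff. The change does not protect VAS or the self-rated CMS items, and does not stop patients volunteering their group. The article describes the study as ongoing, so visits still to come could benefit.
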